### Intervention

2.3

The intervention designed in the AECAP consists of a basic structure and a specific methodology, which will be carried out in the classroom of the San Juan Healthcare Centre in Salamanca.

#### Structure

2.3.1

The material required to perform the formative activity will be an Esaote MyLabSix ultrasound scanner (Esaote Spain, Barcelona, Spain), a Esaote MyLabGamma portable ultrasound scanner, a 56-in. high-resolution TV HDMI connection to the ultrasound scanner, a computer connected to the ultrasound scanners and to the TV, and an examination table.

#### Formative methodology of the AECAP

2.3.2

The ultrasound classroom will be attended twice per month, specifically on the second and fourth Tuesday of each month, from 6 p.m. to 8.30 p.m. At the beginning of each AECAP, the participants will be given the necessary material to complete the ultrasound training individually, following the structure described below.

Basic course in clinical ultrasound (abdomen and thyroid ultrasonography) of a total duration of 30 hours (15 hours of theory and 15 hours of practice). The course will be taught in the first term of 2020.

##### Clinical sessions with patients

2.3.2.1

In this stage, the participants will familiarize with the practical utility of clinical ultrasound through clinical cases with real patients, who agreed to participate by signing an informed consent document. The sessions will be presented as follows: before the patient enters the classroom, the clinical case is presented to the participating physicians, the patient enters the classroom, the ultrasound is carried out with visualization in the TV of the classroom, and the result is written in a report (Fig. 1). All the data will be incorporated to the “case presentation model.” This phase will be conducted from April to October 2020. The teacher of each session will collect the informed consent of the participating patients.

**Figure 1 F1:**
[figure not shown]
Clinical ultrasound training in the primary care clinical ultrasound classroom (AECAP).

##### Final practical lecture

2.3.2.2

During the formative process, all participants will have to present a clinical case in which the use of ultrasound is useful for the diagnosis, and which will be used to assess the formative process. In each clinical case, the following variables will be recorded: relevance of ultrasound in the case, consistency of the results with the clinical data and therapeutic plan, and the need for ultrasound to be carried out by the radiology service or application for other imagery tests (CT, NMR) and endoscopy.

##### Evaluation of the intervention

2.3.2.3

Primary and secondary results.

###### Primary results

2.3.2.3.1

Evaluation of knowledge and skills. An initial evaluation of knowledge will be carried out prior to the beginning of the formative intervention, which will consist of 10 multiple-choice questions with only 1 possible answer (5 theoretical questions about the fundamentals and use of ultrasonography, and interpretation of 5 images of pathologies or ultrasound anatomy). Once the formative sessions and practical lectures begin, a continuous evaluation system will be used, through which the participants will be evaluated by the teachers/instructors, valuing, in a normalized manner, theoretical, practical, and interpretative aspects. For the final evaluation, a new test will be carried out, with 10 questions similar to those of the initial test (5 theoretical questions and 5 common images). Then, a structured valuation will be carried out for the presentation of the final clinical case of each participant. Lastly, the ultrasound examination of 6 patients with common pathologies or normal ultrasound, who have an abdominal or thyroidal ultrasound previously informed by the radiology service, will be evaluated, assessing the consistency of the description, measures, and diagnosis.

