**Methods::**

Quasi-experimental study, with a before/after design, a control group, and 1 year of follow-up. Twenty family physicians working in primary care health centers with a list of over 800 patients will be included, as well as a control group of family physicians with similar characteristics in terms of age, sex, and patient list. A structured training process oriented to the clinical practice of the family physician, primary care clinical ultrasound classroom (AECAP), will be carried out, and the improvement of knowledge and skills of the participants will be evaluated, as well as the improvement of the quality of care based on clinical indicators.

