Therefore, multiple authors and scientific societies of primary care state that the generalized use of ultrasound in the usual practice of family physicians allows making clinical decisions with greater diagnostic precision and reducing the high levels of uncertainties with which these professionals work in the field of healthcare, as well as contributing to reducing the waiting lists of radiology services and shortening the care time in potentially critical situations.^[2,19,20]^

In the scope of primary health care in Spain, the use of ultrasound has been generalized in the healthcare centers of all the autonomous communities, which is also happening in other European countries.^[21]^ This is posing an important effort in the training of family physicians in the use of this tool. Currently, the ultrasound training offered by public and private entities for family physicians in Spain is abundant and of high quality, although it usually has a very academist orientation with little focus on the clinical practice.

The primary care clinical ultrasound classroom (PCCUC) presented by this project aims to provide the participating family physicians with specific training in ultrasound oriented to clinical practice in the scope of primary health care. The PCCUC uses a novel formative system characterized for the valuation and interpretation of clinical cases in real time (clinical session with the patient). Moreover, it includes a 1-year follow-up of the participants in order to assess the utility of this method not only in terms of the knowledge and skills acquired, but also regarding other results of clinical practice.

Therefore, the main objective of the project is to develop an ultrasound training methodology oriented to the clinical practice of family physicians in the scope of primary health care; it also aims to evaluate the effectiveness of such training regarding the increase of knowledge and skills and the improvement of the clinical practice, evaluated by the number of referrals to specialized radiology services, diagnostic waiting time, diagnostic precision, and improvement of the health care provided.

As a secondary objective, the project aims to validate the PCCUC training system for use in the training of undergraduates and post-graduates and in the continuous training of family physicians.

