### Design and scope

2.1

This is a quasi-experimental study with a before/after design, a group control and a 1-year follow-up to evaluate the effectiveness of the formative intervention in clinical ultrasound with family physicians. The control group will consist of family physicians with similar characteristics, who will not participate in the AECAP. The project will be carried out with family physicians who work in Spanish primary healthcare centers.

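### The plan promises an increase in skills, but hands-on scanning has no before-training value and no described control value, so only the level attained can be estimated

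*Protocol article*

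**What the plan says.** The Methods paragraph of the abstract says that "the improvement of knowledge and skills of the participants will be evaluated". The Introduction makes this part of the main objective: to "evaluate the effectiveness of such training regarding the increase of knowledge and skills", alongside improved clinical practice. Section 2.1 describes the study so: "This is a quasi-experimental study with a before/after design, a group control and a 1-year follow-up".

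Section 2.3.2.3.1 places knowledge and skills together under the primary results and sets out the instruments in time order:

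- Before training: "An initial evaluation of knowledge will be carried out prior to the beginning of the formative intervention, which will consist of 10 multiple-choice questions". Its content is "5 theoretical questions about the fundamentals and use of ultrasonography, and interpretation of 5 images of pathologies or ultrasound anatomy".
- During training: "Once the formative sessions and practical lectures begin, a continuous evaluation system will be used". Teachers rate theoretical, practical and interpretative aspects.
- At the end: a second ten-item test of the same make-up, then a structured rating of each participant's clinical case, and then the hands-on examination: "Lastly, the ultrasound examination of 6 patients with common pathologies or normal ultrasound". These patients already have a radiology report, and the physician's description, measurements and diagnosis are compared with it.

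Section 2.4 assigns paired tests to before/after data and kappa to the consistency of diagnoses. Section 2.2 admits only physicians without earlier training in clinical ultrasound.

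**The concern.** An increase is a difference between two values: a later one and either an earlier one in the same people or one in a comparison group. For hands-on scanning the article describes only the later value. A good result in the six-patient examination would show that trained physicians perform well at the end. It would not show by how much the course raised their performance.

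This matters because the outcome is primary and the objective judges the effectiveness of the course by the increase. An analysis plan cannot repair the gap: it can choose a method, but it cannot supply a baseline that was not collected. The limitations in section 3.1 cover attribution, the Hawthorne effect and the imperfect standardization of the continuous evaluation, but not this point.

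**Working it through.** No figure in the article is at issue, and it reports no sample-size or power calculation that bears on the point. The check is to set each primary instrument in section 2.3.2.3.1 against its time points.

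| Instrument | Before training | During | End | Described in controls |
|---|---|---|---|---|
| Written test (5 theory + 5 image items) | yes | no | yes | no |
| Continuous evaluation (includes practical aspects) | no | yes | no | no |
| Final case presentation | no | no* | yes | no |
| Examination of six patients against radiology reports | no | no | yes | no |

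*The case is presented during the training process (section 2.3.2.2) and rated as part of the final evaluation.

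1. **Instruments with a before/after pair:** 1 of 4, the written test. The other three, which are those that touch practical performance, have no value from before training.

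2. **Could the controls stand in for the missing baseline?** Section 2.1 says that they do not take part in the classroom. Section 2.3.2.3.2 names them for the clinical-practice outcomes (radiology requests, referrals, waiting times). Section 2.3.2.3.1 speaks only of participants. No end-of-study scanning comparison is therefore described.

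3. **What can the methods in section 2.4 deliver?** The paired *t* test, Wilcoxon test and McNemar test each need a before and an after value, and among the primary instruments only the written test has both. Kappa describes agreement at one time, not change.

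4. **What the hands-on data do give.** With 20 physicians and six patients each, there are at most 20 × 6 = 120 examinations, on the assumption that every physician scans all six. They support an estimate of agreement with radiology at the end of training.

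5. **What the written test gives.** Five of its ten items are image interpretation at both time points. A before/after comparison of interpretation on paper is thus available from data already planned. On that sub-score one item is 1/5 = 20% of the scale, against 1/10 = 10% on the full test, so it is the coarser measure.

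**The case against.** The strongest reply has three parts.

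First, entrants must have had no previous training in clinical ultrasound, so their scanning skill is presumably low, and a pre-test could well show only a floor effect. Leaving it out is a defensible choice. That stands as a reason for not running the pre-test, but not as a measurement. The article neither states nor uses an assumption of zero skill. Participants work in centres where ultrasonography is available, and some diagnoses could match the radiology report by chance or from clinical context.

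Second, section 2.4 already pairs kappa with consistency of diagnoses and keeps the paired tests for before/after data. Nowhere does the article say that the six-patient examination will be analysed as change. This is correct, and it means that the planned analysis suits the data. The mismatch lies in the objective and the abstract, which claim more than the instrument can give.

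Third, how the written test is scored is commonly left to the analysis plan. That also stands. A reader might infer that only the total of ten will be analysed, so that a gain in theory could pass for a gain in image reading, but nothing in the article says so.

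Two other stronger readings should be set aside. One is that nothing but theoretical knowledge is measured before training: half of the baseline test is image interpretation. The other is that practical skill is assessed only once: the continuous evaluation also rates practical aspects during training, although it gives no pre-training value.

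**Conclusion.** The point holds for hands-on scanning. The objective and abstract promise an increase in skills. The design as described can estimate change in written knowledge and in image interpretation on paper, but for scanning skill only the level reached during and at the end of training.

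Its extent is one of four primary instruments with a before/after pair and three without. The gain in scanning skill cannot be sized in either direction. A reader might be tempted to put percentage points on it by assuming a starting and a final agreement rate, but the article gives neither. The examination is also not a simple normal-or-abnormal call with a known guessing level, since description and measurements are compared as well.

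The conclusion rests on two readings of section 2.3.2.3.1: that its list of assessments is complete as to timing, and that the end-of-training assessments apply to trained physicians only, because no others are named there. The section states the content and timing of each instrument outright, so this is a feature of the design and not a detail left to a fuller document.

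**What to change.** - In the main objective, the abstract and section 2.3.2.3.1, restate the hands-on primary result as agreement with the radiology report attained at the end of training, and not as an increase. Kappa, already named in section 2.4, can serve for the diagnoses.
- Reserve the word improvement for the written test, which has a before value.
- Report the five image items as their own before/after sub-score, so that any claim of better interpretation rests on those items.
- State that low scanning skill at entry is an assumption drawn from the entry criterion and was not measured.

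The cost is a change of wording and one sub-score from data already planned, with no new participants or assessments. The downside is a narrower claim about skills and a five-item sub-score that is noisier than the total. If an increase in scanning skill must be claimed, it needs a hands-on assessment before training, rated in the same way as the final one. That is new data collection.

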###### Secondary results

2.3.2.3.2

Evaluation of results in the clinical practice.

-Number of applications to the radiodiagnosis service: the number of applications of abdominal and thyroidal ultrasound scans sent to the radiology service by the physicians in the PCCUC and those in the control group in the year before and the year after the training process will be studied.-Number of referrals to specialized health care: In the same annual periods, the number of referrals by both groups of family physicians will be valued.-Diagnosis waiting times of physicians of the intervention and control groups for 2 processes, which will be used as indicators of healthcare quality improvement (cholelithiasis and the etiological diagnosis of haematuria). The source of data will be the computerized clinical history of the Health Service of Castilla y León.

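### The written knowledge test uses a different form before and after training, in the same order for every trained physician, so learning cannot be separated from any difference in test difficulty.

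*Protocol article*

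**What the plan says.** Section 2.3.2.3.1 (Primary results) opens with "Evaluation of knowledge and skills". For the written part, "An initial evaluation of knowledge will be carried out prior to the beginning of the formative intervention". This test has ten single-answer multiple-choice questions: five on theory and "interpretation of 5 images of pathologies or ultrasound anatomy". The closing written assessment is described thus: "a new test will be carried out, with 10 questions similar to those of the initial test (5 theoretical questions and 5 common images").

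The other primary components have no pre-training value. Continuous evaluation starts with the sessions, and the clinical case and the six patient examinations come at the end.

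Section 2.4 (Data analysis) assigns a paired t test or Wilcoxon test to quantitative before/after data, at P<.05.

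Three places bear on the control group. The Abstract says that "the improvement of knowledge and skills of the participants will be evaluated". Section 2.1 says: "The control group will consist of family physicians with similar characteristics, who will not participate in the AECAP". Controls are named as measured only under section 2.3.2.3.2 (Secondary results), for example in the count of scan requests "sent to the radiology service by the physicians in the PCCUC and those in the control group".

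Section 3.1 (Methodological limitations) acknowledges problems of attribution, a possible Hawthorne effect and imperfect standardisation of the continuous evaluation. It does not mention the two test forms.

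**The concern.** A paired comparison measures change only if the instrument is the same, or equally hard, at both times. Here the instrument changes at the same moment as the time point, for every physician. If the second set of questions happens to be easier, that appears as learning; if it is harder, real learning is hidden. With only ten items, a difference of one question is a tenth of the scale.

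Part of the main objective is to show an increase in knowledge, and this is the only primary component from which an increase can be calculated. No later analysis plan can repair the confounding, because data collected this way contain nothing that separates the two effects.

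**Working it through.** The plan states no effect size, SD or power for this endpoint, so there is no figure of its own to reproduce.

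**1. What the paired difference estimates.** Let L be the mean learning in points out of 10, and d the mean amount by which the final form is easier (negative if harder). Every trained physician takes form A first and form B last, so

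E(final − initial) = L + d.

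This is one equation with two unknowns. The bias equals d whatever the true L.

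**2. How large it could be.** From the document: n = 20 trained physicians (section 2.2), a paired t test and a significance level of 0.05 (section 2.4). Assumed: a two-sided test, L = 0, d of 0.5 or 1.0 question, and an SD of change of 1.5, 2.0 or 2.5 points. The test statistic is noncentral t with 19 degrees of freedom and noncentrality (d / SD) × √20, where √20 = 4.472.

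| SD of change | d = 1.0: noncentrality | P<.05 | d = 0.5: noncentrality | P<.05 |
|---|---|---|---|---|
| 1.5 | 2.981 | 0.807 | 1.491 | 0.294 |
| 2.0 | 2.236 | 0.565 | 1.118 | 0.186 |
| 2.5 | 1.789 | 0.397 | 0.894 | 0.136 |

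With d = 0 the rate is the nominal 5%.

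**3. Item-level check.** Ten-item binomial scores were simulated with an assumed 40% or 50% correct at baseline, with or without spread in ability (20,000 replicates). The SD of change came out at about 2.0 to 2.2, which makes the lower rows of the table more relevant than the first. With all ten items 10 percentage points easier and no learning, P<.05 occurred in 43% to 48% of trials.

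**4. The other reading of the final images.** The word *common* may mean images of frequent findings, or images shared by both tests. If five items are shared, only the other five can differ in difficulty. The same per-item shift then gives P<.05 in 14% to 16% of trials. Recall of images already seen, which was not modelled, would be added.

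**5. Does counterbalancing work?** With order A then B the expected change is L + d; with B then A it is L − d. The mean of the two order groups is [(L + d) + (L − d)] / 2 = L. In simulation (40% correct at baseline, 10-point shift per item, no learning, 10 physicians per order), the mean spurious gain was 0.00 items. The false-positive rate was 5.0% with form order in the analysis and 3.4% with a plain paired t test. Giving both forms, in the planned order, to an assumed 20 controls and comparing changes gave 5.1%.

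**The case against.** The article is condensed. The final questions are described as similar and keep the same split of five theory and five image items. A full protocol could describe how the forms are matched. A new form is also a reasonable way to avoid recall of identical questions. The physicians must have had no previous ultrasound training and receive a 30-hour course followed by months of clinical sessions, so zero learning is an extreme assumption. The limitations section already concedes that differences may not be due to training alone. The other primary components do not depend on the difficulty of a written form.

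Much of this stands, and it rules out several stronger readings that a reader might infer:

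- **That the final test is easier and the gain inflated.** The wording on images is ambiguous, and nothing shows the direction or size of a difference.
- **That the forms are known not to be equated.** The article only fails to describe equating.
- **That controls are certainly untested.** No sentence says so. It is a well-supported inference from the Abstract and sections 2.1, 2.3.2.3.1 and 2.3.2.3.2.
- **That 81% is an expected false-positive rate.** It needs the smallest assumed SD, a full one-question shift and no learning.

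What the objection does not remove is the fixed order of two different forms. That is a stated design feature, not an omitted detail. The general caveat on attribution does not cover it, and matching forms by content makes equal difficulty more likely without making it checkable.

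**Conclusion.** The point holds for the written test only. Form and time are completely confounded, so the estimated gain is L + d, with d of unknown sign and size. Under the assumptions in the working (20 physicians, no learning, SD of change 1.5 to 2.5), a one-question difference in favour of the final form gives a significant result in 81% to 40% of trials, and half a question in 29% to 14%. If the images are shared between the tests, the bias is smaller but recall enters.

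If training has a large true effect, rejecting zero may be easy in any case. The size of the gain, which matters for validating the method, would still be off by d. This should be fixed, at little cost. It does not invalidate the other primary or secondary results.

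**What to change.** Write both forms before the start. Randomise 10 of the 20 physicians to form A then B and 10 to B then A, and analyse change with form order in the model. State whether any images appear in both forms.

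Both forms must be written anyway, so no items or visits are added. The small downside is that half the class sees each form months before the other half takes it as the final test, so items may be passed on. Collect the forms after the first test and ask physicians not to discuss them.

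Counterbalancing removes the average difference in form difficulty. It does not remove test familiarity or learning in ordinary practice. Giving the same two short tests to the control group at the same dates would address those, at the price of two 10-question tests per control physician. That is an optional supporting comparison; the primary estimate need not change to a between-group contrast.

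If the initial test has already been given in one form, counterbalancing is no longer possible. The report should then say that the gain includes any difference in form difficulty.
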